## Abstract

**Background:**

Provision of mother’s own milk is the optimal way to feed infants, including very low birth weight infants (VLBW, <1500 g). Importantly for VLBW infants, who are at elevated risk of neurologic sequelae, mother’s own milk has been shown to enhance neurocognitive development. Unfortunately, the majority of mothers of VLBW infants are unable to provide an adequate supply of milk and thus supplementation with formula or donor milk is necessary. Given the association between mother’s own milk and neurodevelopment, it is important to ascertain whether provision of human donor milk as a supplement may yield superior neurodevelopmental outcomes compared to formula.

Our primary hypothesis is that VLBW infants fed pasteurized donor milk compared to preterm formula as a supplement to mother’s own milk for 90 days or until hospital discharge, whichever comes first, will have an improved cognitive outcome as measured at 18 months corrected age on the Bayley Scales of Infant Development, 3^rd^ ed. Secondary hypotheses are that the use of pasteurized donor milk will: (1) reduce a composite of death and serious morbidity; (2) support growth; and (3) improve language and motor development. Exploratory research questions include: Will use of pasteurized donor milk: (1) influence feeding tolerance and nutrient intake (2) have an acceptable cost effectiveness from a comprehensive societal perspective?

**Methods/Design:**

DoMINO is a multi-centre, intent-to-treat, double blinded, randomized control trial. VLBW infants (n = 363) were randomized within four days of birth to either (1) pasteurized donor milk or (2) preterm formula whenever mother’s own milk was unavailable. Study recruitment began in October 2010 and was completed in December 2012. The 90 day feeding intervention is complete and long-term follow-up is underway.

**Discussion:**

Preterm birth and its complications are a leading cause long-term morbidity among Canadian children. Strategies to mitigate this risk are urgently required. As mother’s own milk has been shown to improve neurodevelopment, it is essential to ascertain whether pasteurized donor milk will confer the same advantage over formula without undue risks and at acceptable costs. Knowledge translation from this trial will be pivotal in setting donor milk policy in Canada and beyond.

**Trial registration:**

ISRCTN35317141; Registered 10 August 2010.

## Background

Technological advances in the neonatal intensive care unit (NICU) have greatly enhanced the survival rate of very low birth weight (VLBW) infants (<1500 g). In developed countries, more than 90% of infants born <32 weeks gestation now survive initial hospitalization
[1]. Coincident with this improved survival, VLBW birth is an important cause of long-term neurological morbidity in childhood. Interventions which reduce morbidity and promote normal brain development for VLBW infants are thus urgently required
[2,3].

### Neurodevelopmental outcomes of VLBW infants and the role of mother’s own milk

Many VLBW infants show continued neurologic sequelae such as cognitive deficits, academic underachievement, grade failures and the need for remedial assistance during childhood and middle adolescence
[3]. Aside from intracranial lesions associated with preterm birth, factors shown to impact the neurodevelopmental outcome of VLBW infants include gestational age at birth, sepsis, necrotizing enterocolitis (NEC), chronic lung disease, suboptimal nutrient intake or poor growth
[2-8]. Compelling evidence exists to suggest that use of mother’s own breastmilk compared to infant formula during initial hospitalization positively affects the neurodevelopment of VLBW infants during early childhood and beyond
[9-15]. Vohr et al. demonstrated a dose dependent relationship between breastmilk intake for extremely low birth weight infants enrolled in the National Institute of Child Health and Human Development Glutamine Trial. For every 10 mL/kg/day increase in breastmilk intake, there was an associated increase in the Bayley Mental Development Index of 0.53 at 18 months corrected age (CA)
[14] which persisted to 30 months CA
[15]. The impact of this can be seen to be quite dramatic when comparing a baby who received no breastmilk to one who received 150 mL/kg/day which would equate to a difference of 7.5 points.

Mother’s own milk is thought to improve neurodevelopment because it is well tolerated by the VLBW infant, facilitating the transition from parenteral to enteral feeding, and due to its nutrient composition (with fortification as appropriate); both factors resulting in the provision of optimal substrate for brain development. Additionally, mother’s milk, via a myriad of bioactive components such as secretory IgA, lactoferrin and growth factors, protects from morbidities associated with preterm birth (NEC, sepsis, other infections) that are in turn additive risk factors for an adverse neurological outcome
[9,15,16].

### Use of mother’s own milk in the VLBW population

The World Health Organization, the American Academy of Pediatrics and the Canadian Paediatric Society all recommend mother’s own milk as the exclusive source of feeding for infants during their first 6 months of life
[17-19]. Despite the many advantages of feeding mother’s own milk, the majority of mothers of VLBW infants, for a variety of reasons such as illness, stress, mammary secretory cell immaturity and other factors related to preterm birth, are unable to express adequate amounts of milk to exclusively feed their children
[20]. A smaller percentage of mothers choose not to pump their breasts to provide breastmilk.

### Use of pasteurized donor human milk

In North America, preterm formula is increasingly being replaced by pasteurized donor human milk when a supplement to mother’s own milk is required for VLBW infants. Currently there are three non-profit donor milk banks in Canada and eleven in the United States with more in the planning stages
[21]. There is currently one for profit company in the United States that partners with NICUs to provide donor milk. There remains however a paucity of scientific research with respect to pasteurized donor milk use in the NICU.

In a Cochrane systematic review and meta-analysis, Quigley et al. demonstrated both benefits and risks associated with the use of donor milk
[22]. See Table 
1 for a summary of the individual studies included in this review. Importantly, there was a higher incidence of NEC among infants with birth weights < 2500 g and fed formula versus those fed donor milk (relative risk of 2.5 [95% CI, 1.2, 5.1]). Because NEC is the most common gastrointestinal emergency among VLBW infants, its prevention is a powerful argument in favor of donor milk as an alternative supplement to formula when mother’s own milk is not available
[23]. NEC may lead to perforation of the bowel, bowel resection and death or long-term feeding problems associated with a shortened gastrointestinal tract
[23]. Further, NEC, particularly surgical NEC has been shown to be associated with adverse neurodevelopment outcomes at 18–24 months CA
[24].

**Table 1 T1:** Formula milk versus donor milk for feeding preterm or low birth weight infants (Cochrane review)

**Author**	**Year**	**Subjects**	**Comparison**	**Blind**	**Primary outcome**	**Notes**
**Davies**[25]	1977	68 preterm (28–36 weeks)	Term formula vs Donor Milk	No	Slower growth first month for Donor Milk	Uncertain group for 2 infants with mother’s own milk
**Gross**[26]	1983	67 preterm (27–33 weeks)	Term formula vs Donor Milk	No	Slower growth for term Donor Milk (not preterm Donor Milk)	Infants with feed intolerance/NEC withdrawn from growth analysis
**Lucas**[27]	1984	159 LBW (<1850 g)	Preterm formula vs Donor Milk	No	Slower growth for Donor Milk; no neurodevelopmental difference	
**Lucas**[28]	1984	343 LBW (<1850 g)	Preterm formula vs Donor Milk	No	No neurodevelopmental difference	
**Raiha**[29]	1976	106 LBW (<2100 g)	Term formula vs Donor Milk	No	No difference in growth	
**Schanler**[30]	2005	173 preterm (<30 weeks)	Term formula vs Fortified Donor Milk	Yes	Slower growth for Donor Milk, no difference in infection events	Only fortified Donor Milk study; 20% cross-over from Donor Milk to Formula
**Schultz**[31]	1980	20 preterm	Term formula vs Donor Milk	No	No difference in weight gain	
**Tyson**[32]	1983	81 LBW (<1500 g)	Preterm formula vs Donor Milk	No	Slower growth for Donor Milk	Donor Milk not pasteurized; Randomized day 10; 5 affected infants withdrawn

The Quigley et al. review and meta-analysis, however, concluded that infants fed donor milk experienced slower weight (*p* < 0.0001), length (*p* < 0.0003) and head circumference (*p* < 0.0001) gains than those fed formula. These risks associated with donor milk are of significant concern because VLBW infants are born with impoverished nutrient reserves, and are subject to metabolic stresses that further elevate nutritional requirements
[22,23]. Nutrient deficits and sub-optimal growth has significant long term neurodevelopmental consequences
[2,23,24,33,34].

Quigley et al. point out that all but one of the randomized controlled trial (RCTs) examined in their meta-analysis were >25 years old when smaller VLBW infants did not survive. Feeding practices have also since changed to include preferential use of mother’s own milk along with nutrient fortification of human milk to promote adequate growth. There was only one RCT
[30] in the Cochrane review that was reflective of current clinical practice which includes much smaller babies, preferential use of mother’s own milk and nutrient fortification. This study however did not look at long-term neurocognitive outcomes.

### Effects of the pasteurization process

The donor milk used in North American NICUs is typically pooled from 3 or more mothers to reduce batch-to-batch variability in nutrient composition and is pasteurized (Holder pasteurization, 62.5°C for 30 minutes) according to Human Milk Banking Association of North America (HMBANA) guidelines to prevent the transmission of infectious agents (e.g. HIV, pathogenic bacteria
[35]). Despite pooling, donated milk often contains a lower concentration of energy, protein, fatty acids and other nutrients compared to mother’s own milk due to the fact that the donations usually come from mothers who deliver a healthy term infant several weeks or months after delivery once they have accrued a surplus of pumped milk
[36-38]. It is well known that the concentration of a number of nutrients, most especially protein, are higher in the breastmilk of mothers delivering preterm compared to that of mothers of term born infants
[39,40]. Further, the concentration of many nutrients in breastmilk decline with the progression of lactation
[39]. While many nutrients are unaffected, Holder pasteurization will impact the concentration of some nutrients in breastmilk, most notably a number of the water soluble vitamins (e.g. folate and vitamin C)
[41,42] (Table 
2). Further, donor milk, compared to mother’s own milk, also undergoes at least one additional collection/storage container transfer and freeze-thaw cycle, as part of the pasteurization process affecting the concentration of many nutrients in breastmilk as fat adheres to the walls of each vessel
[39].

**Table 2 T2:** Breastmilk components and the effect of pasteurization

**Component**	**Effect**	**References**
Adiponectin	33% reduction	[43]
Amylase	15% loss of activity	[44]
B-cells, T-cells	Abolished	[45,46]
Bile salt dependent lipase	Abolished	[44]
CD14 (soluble)	88% reduction	[47]
Fats:		
Total fat	No effect	[48-50]
C14:1-C24:1	No effect	[44,49]
C8:0-C24:0	No effect	[44,49]
n-3,n-6 PUFA	No effect	[44,49]
AA, DHA	No effect	[44,49]
Linoleic, linolenic	Reduced	[51]
Calcium	No effect	[48]
Copper	9% reduction No effect	[50,52]
Escherichia coli inhibition	26% reduction	[53]
Epidermal growth factor	No effect	[54,55]
Erythropoeitin	Significantly reduced	[56]
Folate	16-31% reduction	[41,42]
Free fatty acids	80% increase	[57]
Gangliosides	No effect	[54]
Hepatocyte growth factor	60% reduction	[54]
Immunoglobulins:		
IgA, sIgA	0-48% reduction	[45,46,48,58-62]
IgG	34% reduction	[60]
IgM	Abolished	[61,62]
Insulin	46% reduction	[43]
IGF-1, IGF-2, IGF-BP2,3	7-39% reduction	[55]
IL-1β, IL-10	Significantly reduced	[54,56]
IL-2, Il-4, IL-5, IL-12, IL-13	No effect	[54]
IL-8	Increased	[54]
Interferon gamma	Significantly reduced	[54]
Iron	0-15% reduction	[50,52]
Lactate	7% reduction	[57]
Lactoferrin	57-80% reduction	[58,60,61]
Lactose	No effect	[48,50]
Lipoprotein lipase	Abolished	[44]
Lysine	Significantly reduced	[61,63]
Lysozyme activity	No effect 24-60% reduction	[58-62]
Lymphocytes	Abolished	[46]
Magnesium	No effect	[48]
Mannose-binding lectin	No effect	[47]
Oligosaccharides	No effect	[64]
Phosphorus	No effect	[48]
Potassium	No effect	[48]
Protein	No effect Reduced	[43,48,50,62]
Sodium	No effect	[48,50]
TGF-α, TGF-β	No effect Reduced	[54,65]
Vitamin A	No effect	[50]
Vitamin B6	15% reduction	[42]
Vitamin C	36% reduction	[42]
Zinc	0-3% reduction	[50,52]

Modified with permission from: Ewaschuk JB, Unger S, Harvey S, O’Connor DL, Field CJ. Effect of pasteurization on immune components of milk: implications for feeding preterm infants. Applied Physiology, Nutrition, and Metabolism 36:175–182, 2011.

Very little is known about the impact of the pasteurization process on the myriad of bioactive components in human milk, many of which serve a dual role in nutrient absorption and as anti-infective agents
[66]. Holder pasteurization reduces the concentration of immunoglobins (secretory IgA, G and M)
[48,58,67]. Live cellular components, including B and T lymphocytes are eliminated (Table 
2). Of the few enzymes that have been studied, milk amylase is relatively unaffected, lysozyme in more recent reports has been shown to be affected and lipases are completely denatured
[44,48,58,59,67]. Fat absorption is lower in donor versus mother’s own milk-fed infants, presumably due in part to destruction of bile salt stimulated lipase known to compensate for low intraluminal lipase activities necessary for fat absorption
[68]. Lactoferrin, an anti-microbial and immunomodulatory iron-binding glycoprotein shown in both animal studies and a recent clinical trial to be effective against neonatal sepsis is reduced by 80%
[58,69,70]. Immune modulators known to be important in NEC prevention such as IFN-γ, TNF-α, IL-1β. IL-10 and hepatocyte growth factor remain present in donor milk post pasteurization however in significantly reduced quantities
[54].

### Study objectives

The primary question is whether the use of pasteurized donor milk, compared to preterm formula, as a supplement to mother’s own milk for the first 90 days after randomization or until hospital discharge, whichever comes first, improves cognitive development of VLBW infants at 18 months corrected age as measured by the Bayley Scales of Infant Development, 3^rd^ edition (BSID). Secondary questions are whether donor milk will reduce a composite of death and serious morbidity (NEC, late onset sepsis, chronic lung disease and severe retinopathy of prematurity); support growth; and improve language and motor development at 18 months corrected age. Exploratory research questions include: will use of donor milk, as a supplement to mother’s own milk: (1) influence feeding tolerance and nutrient intake (2) have an acceptable cost effectiveness (medical and non medical) from comprehensive societal perspective?

## Methods/Design

This is a pragmatic multi-centre, double-blind, RCT designed to evaluate the effectiveness of pasteurized donor milk as a supplement to mother’s own milk in those infants when mother’s own milk is unavailable. The analysis will be conducted using an “intention to treat” approach. Infants randomized to the intervention group received donor milk when mother’s own milk was unavailable. Infants randomized to the control group received formula designed for preterm infants when mother’s own milk was unavailable.

Funding was received from the Canadian Institutes for Health Research (MOP#210093), SickKids Foundation and the Ministry of Health and Longterm Care of Ontario. Infants were recruited in one of four participating level III NICU in Toronto and Hamilton, Canada. A comprehensive list of parental and infant demographic variables was collected after written informed consent was secured (Table 
3). Randomization, performed within 96 hours of birth, was done centrally using a 24 hr/day web-based third party randomization service (Centre for Mother Infant and Child Research, Toronto). The study allocation was randomly assigned in a ratio of 1:1, in random blocks of 4 and 8, with stratification by centre and birth weight grouping (<1000 g and 1000–1499 g). Aside from the research dietary technicians assigned to the study and a single neonatal dietitian, all members of the research study team (including outcome assessors), clinical teams and families are blinded to study allocation.

**Table 3 T3:** Demographic variables collected during the DoMINO trial

**Infant characteristics**	**Prenatal and parental characteristics**
Gestational age at birth+	Gravity/Parity*
Birth weight, length and head circumference+	Artificial reproductive technology (type and origin of eggs, sperm)+
Size for gestational age (small [SGA], appropriate [AGA] or large for [LGA] gestational age)+	Antibiotic use prior to delivery (prior 2 weeks)+
Sex+	Use of Prenatal Steroids+
Multiple birth status+	Cesarean delivery*
5-minute Apgar score+	Mom has previously breastfed (yes/no)*
Newborn Illness severity score (SNAP-II+)	Mom intends to breastfeed (yes/no)*
	Parental education (highest degree or diploma attained)*
	Parental weight and height (self-reported)*
	Parental age*
	Number of children in current household*
	Smoking (maternal history during pregnancy)*
	First language spoken in the home*
	Socioeconomic status (single parenting; above or below poverty line)*
	Ethnicity*

Baseline demographic variables collected by means of parental interviews* or from medical records +.

The feeding intervention continued for 90 days including transfer to a participating level II unit or until discharge home, whichever occurred first. Other than whether infants received donor milk or preterm formula as a supplement, all other aspects of feeding were directed by the clinical team at each NICU. General feeding guidelines were agreed upon by the participating NICUs to provide a consistent approach, and to set criteria necessitating removal from the feeding protocol. These detailed guidelines are found in Table 
4. Donor milk was purchased and shipped primarily from the Mother’s Milk Bank of Ohio (>95%) with backup from Calgary Mother’s Milk Bank, both HMBANA members. Donor milk from Ohio was collected and pooled from at least three women who had delivered within the previous three months. Once nutrient fortification of donor milk commenced, a protein module (0.3 g/dl, Beneprotein, Nestle) was added to donor milk to bring the analyzed protein content (0.9 g/dl) up to the average estimated protein concentration of mother’s own milk after 30 days (1.2 g/dl)
[71,72].

**Table 4 T4:** Feeding guidelines

	**Supplement to MOM**	**Supplement to MOM**
	Pasteurized Human Donor Milk	Preterm Formula*
		Similac Special Care 20 or 24 kcal/ oz [3.0 g protein/100 kcal] [Abbott Laboratories] or
		Enfamil Premature Formula 20 or 24 kcal/oz [3.0 g protein/100 kcal] [Mead Johnson Nutritionals]
**Initiation of enteral feeding**	Day 1-7	Day 1-7
**Volume of feeding at initiation**	10-20 ml/kg/d (hold volume for 3-5 days)	10-20 ml/kg/d (hold volume for 3–5 days)
**Rate of feed advancement**	10-25 ml/kg/day	10-25 ml/kg/day
**Fortification to commence at >120 ml/kg/day using milk pumped > 7 days after parturition+**	Human milk fortifier	Not Applicable
	Enfamil Human Milk Fortifier, [Mead Johnson Nutritionals] or	
	Similac Human Milk Fortifier, [Abbott Laboratories]	
**Volume**	140-200 ml/kg/d to achieve a weight gain of > 15 g/kg/day	140-200 ml/kg/d to achieve a weight gain of > 15 g/kg/day
**Minimum protein dose to be provided once (or up to 3 days after) volume reaches >150 ml/kg/d**	3.0 g/kg/d**	3.0 g/kg/d**
**At 24 kcal/oz and weight gain < 15 g/kg/d for 3–7 days**	Concentrate feeding using a multi-nutrient modular to 26–27 kcal/oz	Modular to 26–27 kcal/oz
**At 27 kcal/oz and weight gain < 15 g/kg/d for 3–7 days**	Concentrate feeding using a multi-nutrient modular to 30 kcal/oz	Concentrate feeding using a multinutrient modular to 30 kcal/oz
**At 30 kcal/oz and weight gain < 15 g/kg/d for 3–7 days**	Remove from feeding protocol	Remove from feeding protocol

*A low or high iron formula will be used for study infants at each NICU depending on the iron content of the human milk fortifier in use to avoid unblinding of feeding assignments.

+Commence supplementation with 200–400 IU vitamin D and 2–4 mg/kg/d elemental iron.

**As infants approach their estimated date of delivery and/or readied for hospital discharge intakes will usually be below this value.

Each morning, a member of the health care team at each NICU completed and FAXed in a feeding order for study infants in their care to our research diet technicians. All study feeds for research participants were prepared in a single milk preparation room at the Hospital for Sick Children in a laminar flow cabinet. Feeds were delivered to units daily in amber single-use oral syringes (Baxa, Deerfield Illinois) or orange plastic wrapped bottles by study staff or courier. The contents of syringes and bottles were indistinguishable by visual inspection.

The frequency and duration of assessment during the feeding intervention and after hospital discharge are illustrated in Figure 
1. During the feeding intervention, morbidity/mortality, growth, feeding tolerance, nutrient intake data and level of respiratory support (daily acuity index proxy) were extracted prospectively from the medical record or directly assessed on a weekly basis by a member of the study team. Following discharge home, infants are seen at clinic visits scheduled at 4, 8, 12 and, 18 months CA corresponding to important feeding, growth and developmental milestones. Additionally, families are called monthly after discharge to ascertain healthcare resources accessed on behalf of the child (e.g. visiting a pediatrician, home care). During these calls, information on current feeding practices is collected as these (e.g. duration of breastfeeding) may influence neurodevelopment.

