### Statistical analyses

Using a 5 point difference in composite cognitive scores at 18 months CA, with 80% power (alpha level of 0.05), and an estimated standard deviation in each feeding group of 15, we estimated that we required 142 infants in each feeding arm. We assumed a 10% loss to follow-up during the feeding intervention and an additional 10% loss to follow-up after discharge, thus necessitating 176 infants to be randomized in each of the two feeding groups. As the number of infants withdrawn from the study exceeded 10%, primarily due to infant death, we overenrolled by 11 subjects to produce a final sample size of 363 subjects.

Analyses will be carried out using SAS Version 9.1 (SAS Institute, Cary, NC, USA). Descriptive statistics will be calculated for all variables of interest. Continuous measures will be summarized using means and standard deviations whereas categorical measures will be summarized using counts and percentages. The primary analysis for this intent-to-treat study will include all infants as randomized, regardless of adherence with the feeding protocol. The initial analysis will be a comparison of means (cognitive composite score) between the 2 groups at 18 months CA. A generalized linear model will carry out this comparison, controlling for length of treatment and adjusting for correlation of observations taken at the same centre. Sex, birth weight strata (<1000, 1000–1499 g), use of antenatal steroids, multiple birth, a count of key morbidities and duration of mother’s own milk-feeding are prognostic of neurodevelopmental outcome, and for this reason we will perform a secondary analysis which will include a regression model adjusted for the aforementioned characteristics
[4,6,13].

Children who cannot be tested on the BSID-III due to disability, severe delay or who perform below the threshold of the test for individual composite scores (cognitive, language motor) will be assigned a score of 49
[7]. The scores will be computed by trained individuals who have established inter rater reliability (R^2^ = 80) and who are blind to study group. Other missing data will be handled using methods of multiple imputation.

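### Birth-weight stratum is used to randomise and is called prognostic, but it is left out of the primary model, which mildly weakens the primary test if its standard error is model-based

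*Protocol article*

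**What the plan says.** Under Methods/Design, equal numbers are to be allocated to the two arms. The article describes the allocation as made "in random blocks of 4 and 8, with stratification by centre and birth weight grouping". The birth-weight groups are <1000 g and 1000–1499 g, and there are four recruiting centres.

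Under Statistical analyses, "The initial analysis will be a comparison of means (cognitive composite score) between the 2 groups at 18 months CA". This is done with a generalized linear model, "controlling for length of treatment and adjusting for correlation of observations taken at the same centre". Birth-weight stratum is not among its terms.

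The same section then lists sex, birth-weight strata, antenatal steroids and multiple birth, and continues that these together with "a count of key morbidities and duration of mother’s own milk-feeding are prognostic of neurodevelopmental outcome". For that reason "we will perform a secondary analysis which will include a regression model adjusted for the aforementioned characteristics". Birth-weight stratum appears only in this secondary analysis.

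**The concern.** Of the two factors that restrict the randomisation, one (centre) is carried into the primary model and the other is not, although the article calls the omitted one prognostic. Blocking within strata makes the two arms nearly equal in their mix of birth weights, so the real sampling variance of the treatment difference contains almost none of the variance between strata. A model without the stratum still counts that variance as residual noise. Its model-based standard error is then larger than the true one, and part of the precision that stratification bought is not used.

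The secondary regression does not fill the gap cleanly. It also adjusts for a morbidity count and for duration of mother's-own-milk feeding. Both arise after randomisation, and serious morbidity is itself part of a secondary outcome. The article therefore describes no analysis of the primary outcome that adjusts for birth-weight stratum on baseline variables alone.

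**Working it through.** **Inputs from the article (Statistical analyses).** Difference 5 points, power 80%, alpha 0.05, "an estimated standard deviation in each feeding group of 15", 142 evaluable per arm, 176 randomised per arm.

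**Assumptions, not in the article.** Score gap D between the strata of 4 to 10 points; share p of infants in one stratum of 40–50%. Total SD is held at 15.

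**Reproducing the plan's figures.** Two-sided, n = 2(1.960 + 0.842)² × 15²/5² = 141.3, so 142 per arm. With two successive losses of 10%, 142/(0.9 × 0.9) = 175.3, so 176. Both agree with the article.

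**Formulas for omitting the stratum (model-based SE, no length-of-treatment term).**
- Share of variance due to the stratum: R² = p(1−p)D²/15².
- SE that the model reports: SE₀ = 15√(2/142) = 1.780.
- True SE under stratified allocation, which is also the SE with the stratum fitted: SE₁ = SE₀√(1−R²).
- Actual type I error: 2[1 − Φ(1.96 × SE₀/SE₁)].
- Power without the stratum: Φ[(5 − 1.96 × SE₀)/SE₁].
- Power with the stratum: Φ[5/SE₁ − 1.96].

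| D, p | R² | SE₁ | SE₀ too wide by | Type I error | Power without | Power with |
|---|---|---|---|---|---|---|
| 4, 0.4 | 0.017 | 1.765 | 0.9% | 4.8% | 80.4% | 80.9% |
| 5, 0.5 | 0.028 | 1.755 | 1.4% | 4.7% | 80.5% | 81.3% |
| 10, 0.5 | 0.111 | 1.678 | 6.1% | 3.8% | 81.6% | 84.6% |

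The fair comparison is between the last two columns. Under stratified allocation the unadjusted test already has slightly more than the nominal 80%, so the loss is 0.5 to 3.0 points.

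**Simulation check.** 284 infants, four centres, two strata, permuted blocks of 4 and 8. With a 10-point gap and no length-of-treatment term, the model-based SE exceeded the empirical SD by 4–7%. With the stratum fitted, the ratio was about 1.00 (0.98 to 1.01).

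**Adding length of treatment.** With a 10-point gap and an assumed 30-day difference in treatment length between strata (before the 90-day cap), the mean SE was 1.741 without the stratum and 1.681 with it. That is 1.741/1.681 − 1 = 3.6% wider, against about 6% without length of treatment. Measured against that model's own sampling SD, the excess was only about 1–2% (ratios 1.007 and 1.020 in two runs), with a rejection rate of 5.0% under the null. In this scenario what remains is mainly lost power: 82.0% without the stratum against 84.2% with it.

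**Clustered standard error.** Same set-up, 10-point gap, length of treatment left out: empirical SD 1.67, model-based SE 1.78. A centre-clustered sandwich SE was 1.66 with a 4/3 small-cluster factor and 1.44 without it.

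**The case against.** Four points can be made for the plan.

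1. **The direction depends on an estimator that the article does not name.** Adjusting for correlation within centre could mean a clustered sandwich error. Blocking is within centre and stratum, so the stratum largely cancels within each centre, and such an error need not be too wide. With four clusters and no small-sample factor it came out too narrow. This stands, and the claim is limited to model-based errors.

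2. **Length of treatment may track birth weight and take up part of the excess.** This stands as to size. It does not make length of treatment a substitute for the stratum, because it is observed after randomisation and may itself depend on the feeding arm.

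3. **The effect is small and in the safe direction.** This stands. A reader might infer that a design factor missing from the model puts the validity of the primary test at risk, or that the omission costs the whole step from 80% to about 84–85% power. Neither follows. With a model-based error, omitting the stratum creates no excess of false positives, and the correct baseline for power is 80.4–81.6%.

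4. **A stratum-adjusted analysis is already planned.** This stands in part. Because the article reports that withdrawals exceeded 10%, mainly through death, a reader might infer that losses below 1000 g unbalance the arms with nothing to correct it. The article does not support that. Losses must also differ by arm to cause imbalance, its text reports no losses by stratum or arm, and it plans both the secondary regression and multiple imputation. That regression is still not a clean stratum-adjusted estimate, because it mixes in post-randomisation variables.

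**Conclusion.** The point holds as a modest matter of efficiency and of matching the analysis to the design. The article stratifies by birth weight, calls it prognostic, and fixes a primary model without it. For assumed gaps of 4–10 points and a 40–50% split, with a model-based SE, 142 per arm and length of treatment ignored, the SE is about 1–6% too wide, type I error is about 4.8–3.8%, and 0.5–3 points of power are lost. Near a 5-point gap the cost is under 1 point of power. The loss may be smaller once length of treatment is in the model, and the excess width may not appear with a centre-clustered error. The stated sample size is not affected. The change is worth making because it costs almost nothing, not because the planned test is invalid.

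**What to change.** Add birth-weight stratum (<1000 g, 1000–1499 g) to the primary model as a fixed effect beside centre, so that the analysis conditions on both randomisation factors. State at the same time whether the standard error is model-based or clustered by centre.

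The cost is one model term. The variable is known at randomisation, needs no new data and does not change the sample size. Recruitment and the feeding intervention are complete, but follow-up is still underway and the outcome assessors are blinded. The change should therefore be recorded as a dated amendment before unblinding. Whether length of treatment should stay in the primary model is a separate question, and the stratum term is justified either way.
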